### Sample Size Calculation

For the sample size calculation, we relied on a meta-analysis [19] of a smartphone app–based weight loss intervention. We applied –1.5 (95% CI –2.09 to –1.09) kg as the clinically meaningful difference between the 6-month smartphone-only intervention without face-to-face motivational interviewing and the control group, as indicated in the meta-analysis. However, the meta-analysis did not provide SD values, so we used the SD (–1.8, SD 3.7) [37] value of the smartphone self-monitoring–only intervention results as a reference and set the expected value at –1.5 (SD 3.7) kg. Furthermore, the α error was set at 5% (95% CI=1.96), power (1 – β error) at 80% (0.842), and the dropout rate at 10%. Based on the above values and after consulting a statistical expert, the sample size was calculated to be 108 individuals for each group (N=216 in total).

### Assignment, Allocation Concealment, and Blinding

The random assignment will be performed using the permuted block method. Stratification will be conducted based on BMI (threshold: 32 kg/m^2^) and age (threshold: 45 years), which represent the median values reported in a previous study. The four resulting strata will be as follows: (1) BMI ≥32 and age ≥45 years, (2) BMI ≥32 and age <45 years, (3) BMI <32 and age ≥45 years, and (4) BMI <32 and age <45 years.

The list of potential participants recruited was sent to study member allocator 1 in Japan. Allocator 1 prepares a provisional ID list that does not contain attributes other than BMI and age to ensure concealment and sends it to allocator 2. Allocator 2 creates an allocation table with an allocation ratio of 1:1 and BMI and age as adjustment factors using software for randomized controlled trial–stratified substitution blocks and allocates the provisional IDs to each stratum in descending order of provisional ID numbers, from top to bottom.

This study will be conducted in an unblinded manner. This is because the intervention group will be given a scale and an app to be installed; therefore, blinding of the participants will not be possible. In addition, the content of the questions asked during each evaluation differs between the intervention and control groups, making blinding difficult for supporters and research team members.

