### Data Collection Methods

Data will be obtained from supporters visiting the market to conduct face-to-face structured interviews (Multimedia Appendix 1) and anthropometric measurements. Body measurements will be taken at the time of recruitment to measure height and weight, and BMI will be calculated immediately. Subsequent data collection will include weight measurements, body fat percentage, and abdominal circumference. Height will be measured using a hardware SHUREMAN Lock Convex measuring tape (Kenoh Co, Ltd, Japan, model LC-5525) with a locking function, and an InBody (InBody Japan Inc, model H20N) will be used as the body composition scale. Structured interviews will be conducted using a questionnaire asking about sociodemographics, weight perception, behavioral change stages related to weight loss, behaviors related to weight management, body pain level (using the VAS scale), and the use of smartphone apps for weight management.

In addition, the intervention group will be asked about the weight and behavioral change stages of exercise and diet during the monthly telephone intervention.

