### Statistical Methods

The primary outcome will be evaluated by comparing the difference in weight change between the intervention and control groups 6 months after the intervention ended. In addition, the effectiveness of the weight loss intervention will be estimated using a linear regression model with weight change at 6 months as the dependent variable and the affiliation group, stratification variables, and other sociodemographic attributes as covariates.

Among the secondary outcomes, weight, body fat percentage, abdominal circumference, and degree of body pain (VAS scale) will be measured and compared in the same way as the primary outcome at all evaluation periods (3, 6, and 12 months). Other secondary outcomes will be compared to differences in rates at baseline and 3, 6, and 12 months. These analyses will follow the intention-to-treat principles. Additionally, intention-to-treat and per-protocol analyses will be performed and compared to address cases of protocol noncompliance.

Within the intervention groups, weight loss will be used as the dependent variable, and linear regression model analyses will be performed to estimate the impact of self-monitoring input frequency, WhatsApp group participation, and sociodemographic characteristics as covariates.

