### Data Management and Monitoring

All data will be collected on paper, entered into an Excel data entry format, and stored as digital data. The reason for this is that the intervention in this study involved self-monitoring of weight by app and encouraging behavioral change, so no significant safety issues are foreseen [38,39].

The research team will create a participant management sheet and continuously monitor the participants’ health and weight loss status during the supporters’ calls to identify any problems. During the study period, supporters will hold web-based meetings with the research team 1-6 times a month to share the participants’ situation, which will facilitate the detection of unexpected adverse events.

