### Limitations

First, the intervention cannot be blinded to the participants because those in the intervention group will receive a weighing scale. It is also difficult to make the supporters blinded because the questionnaires are different between the two groups. Second, it is not possible to perfectly prevent the participants from exchanging information with each other. However, we will try to understand the status of communications between the two groups by including a related question in the questionnaire. Third, the target population of the study may not represent all female merchants in Côte d'Ivoire as we only included those who have smartphones. However, as the smartphone ownership rate among female merchants in the market in the previous study was 77% [8], we judged this to be feasible.

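### The reason given for not blinding research team members does not reach whoever cleans and analyses the weights, so coded arms are feasible for the primary analysis

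*Protocol article*

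**What the plan says.** Under Assignment, Allocation Concealment, and Blinding, the protocol article states: "This study will be conducted in an unblinded manner". No role is excepted. Two reasons follow. Participants cannot be blinded because the intervention group visibly receives a scale and an app. For staff, the reason is that the evaluation questions are not the same in the two arms, "making blinding difficult for supporters and research team members".

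The Limitations section returns to the subject and names a narrower group: "It is also difficult to make the supporters blinded because the questionnaires are different between the two groups". It gives no reason for the research team.

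Four other statements bear on the point:

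- **Data Collection Methods:** "Data will be obtained from supporters visiting the market to conduct face-to-face structured interviews", and the same visits include the body measurements.
- **Data Management and Monitoring:** "All data will be collected on paper, entered into an Excel data entry format, and stored as digital data".
- **Statistical Methods:** the weight-change regression includes group, the stratification variables and further sociodemographic attributes that are not named. The analyses follow intention to treat. In addition, "intention-to-treat and per-protocol analyses will be performed and compared to address cases of protocol noncompliance".
- **Ethical Considerations:** access to the data is limited to the research team, which is the group described as hard to blind.

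**The concern.** The scope of the statement is wider than its reasons. A visible scale and arm-specific questions explain why participants, supporters and anyone in contact with them know the arm. They do not explain why the person who cleans and analyses the weights must know it.

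The primary outcome is a difference between two weights per woman, each written on paper and then typed. Two kinds of decision can move its estimate after the data exist: how an implausible weight is queried or resolved, and which covariates enter the model. If the person deciding sees the arms, a reader of the results cannot rule out that the arm influenced the decision. Participants and supporters cannot be masked here, but the analysis can be, so the protection should not be given up by a broadly worded sentence.

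**Working it through.** **1. Does the reason cover the scope?**

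| Role | Reason in the blinding section | Reason in Limitations | Does it prevent masking? |
|---|---|---|---|
| Participants | Scale and app | Scale | Yes |
| Supporters | Questions differ by arm | Questionnaires differ by arm | Yes, in practice |
| Team members in contact with participants or supporters | Questions differ by arm | None | Yes, in practice |
| Person cleaning and analysing weights | No separate reason; at most included among research team members | None | No, if the file holds only ID, coded arm, weights, stratum and baseline covariates |

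The file has to be restricted. Table 2 shows telephone weights and behaviour stages for the intervention group only, and the Outcome section lists app and WhatsApp measures for that group only. A full data set would reveal the arm. Weights at 0, 3, 6 and 12 months are taken in both arms and would not.

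**2. The plan's own figure.** Inputs from Sample Size Calculation: difference 1.5 kg, SD 3.7 kg, z-values 1.96 and 0.842, dropout 10%.

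- Normal approximation: n = 2 × [3.7 × (1.96 + 0.842) / 1.5]² = 95.5, so 96 per group; 96 / 0.90 = 106.7, so 107.
- t-test: 96.5, so 97 per group; 97 / 0.90 = 107.8, so 108.

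The stated 108 reproduces. Masking the analyst enters none of these inputs, so it stays at 108.

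**3. How sensitive is the estimate to a few arm-aware decisions?** Assumptions (not in the documents): no true effect, 97 analysed per arm, normal weight changes with SD 3.7 kg. The single most unfavourable change is removed in each arm: the largest gain in the intervention arm and the largest loss in the control arm. Then two per arm are removed.

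- The largest of 97 normal values lies on average 2.50 SD from the mean, and the second largest 2.14 SD.
- One per arm: shift = 2 × 2.50 × 3.7 / 96 = 0.19 kg.
- Two per arm: shift = 2 × (2.50 + 2.14) × 3.7 / 95 = 0.36 kg, and 0.36 / 1.5 = 24% of the planned difference.
- Simulated two-sided type I error (20,000 null trials): 7.1% for one per arm and 12.3% for two. A separate run of 40,000 gave 5.1% with none removed, 7.2% with one and 11.9% with two.

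**4. The same question for the open covariates.** Assumptions: no true effect, 97 per arm, four candidate covariates that jointly explain 5% to 30% of the variance in weight change, and the smallest p-value taken over all 16 subsets (3,000 simulations per setting). Type I error is about 7% to 12%, against about 4% to 5% with the full set fixed in advance.

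Both exercises describe deliberate selection in one direction. They are upper illustrations of how few decisions matter at this sample size, not forecasts.

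**The case against.** **A reader might infer that every team member is unblinded and that cleaning and modelling will be done with the arms visible.** The article does not say so. It calls blinding difficult, does not write that all team members know the arm, and never mentions the analyst or data cleaning. Only the possibility is supported.

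**Coded arms, query rules, the covariate list and the per-protocol rule may be in the full protocol or an analysis plan that is not shown.** This stands, and their absence from an article is no finding. What remains is that the article takes a position on blinding the research team whose reason does not carry it, and which a masked-analyst provision elsewhere would contradict. Fixing covariates and rules before the data are seen would also remove most of the risk, even with an unmasked analyst.

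**A reader might infer that per-protocol exclusions can move the primary result.** They cannot: the primary comparison follows intention to treat, and the per-protocol analysis is additional.

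**The simulated deletions are extreme.** This also stands. Nothing in the article permits removing valid weights. Paper records and repeated weighings help to resolve outliers without reference to the arm.

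**Masking is not free, and the key cannot rest with the second allocator alone.** Correct. Supporters need the allocation to deliver the intervention. The team also follows participants through the supporters' calls and meets supporters one to six times a month, so those members learn the arm.

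**The larger bias is elsewhere.** Unblinded supporters take the weights, and masking the analyst leaves that untouched. This limits the priority of the point but does not answer it.

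**Conclusion.** The point holds as a low-cost improvement. The blinding statement is broader than its reason, and the article's own Limitations section supports only the narrower version. With covariates unnamed and weights hand-entered, choices affecting the primary estimate could be made with the arms visible; the documents do not show that they will be. The size cannot be estimated from the documents. The 7% to 12% type I error, and the shift of 0.19 to 0.36 kg from deletions, rest on the stated assumptions and mark a worst case. The sample size, alpha and planned power are unaffected.

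**What to change.** - In Assignment, Allocation Concealment, and Blinding, limit the statement to participants, supporters and team members in contact with them.
- State that the primary-endpoint file (ID, weights measured in both arms, stratum, baseline covariates asked of both arms) goes to the analyst with arms coded X/Y. The decoding key is withheld from the analyst; the field team keeps the allocation it needs for delivery.
- Resolve weight queries and fix the covariates and the primary model on that file before decoding, preferably before any comparison between X and Y is run, because a visible difference may hint at which arm is which.
- Fix the per-protocol rule before the 6-month weights are opened, and apply it without sight of outcome weights. Masking the arm is not feasible there, because adherence data exist mainly in the intervention arm.

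**Cost:** protocol wording, a second restricted data file with app, WhatsApp and telephone data held separately until decoding, and an existing team member not involved in participant monitoring to do the primary analysis. If no such member is available, an analyst would have to be found. The change does not reduce bias from unblinded measurement by supporters, which should remain stated as a limitation.

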### Data Collection Methods

Data will be obtained from supporters visiting the market to conduct face-to-face structured interviews (Multimedia Appendix 1) and anthropometric measurements. Body measurements will be taken at the time of recruitment to measure height and weight, and BMI will be calculated immediately. Subsequent data collection will include weight measurements, body fat percentage, and abdominal circumference. Height will be measured using a hardware SHUREMAN Lock Convex measuring tape (Kenoh Co, Ltd, Japan, model LC-5525) with a locking function, and an InBody (InBody Japan Inc, model H20N) will be used as the body composition scale. Structured interviews will be conducted using a questionnaire asking about sociodemographics, weight perception, behavioral change stages related to weight loss, behaviors related to weight management, body pain level (using the VAS scale), and the use of smartphone apps for weight management.

In addition, the intervention group will be asked about the weight and behavioral change stages of exercise and diet during the monthly telephone intervention.

### Statistical Methods

The primary outcome will be evaluated by comparing the difference in weight change between the intervention and control groups 6 months after the intervention ended. In addition, the effectiveness of the weight loss intervention will be estimated using a linear regression model with weight change at 6 months as the dependent variable and the affiliation group, stratification variables, and other sociodemographic attributes as covariates.

Among the secondary outcomes, weight, body fat percentage, abdominal circumference, and degree of body pain (VAS scale) will be measured and compared in the same way as the primary outcome at all evaluation periods (3, 6, and 12 months). Other secondary outcomes will be compared to differences in rates at baseline and 3, 6, and 12 months. These analyses will follow the intention-to-treat principles. Additionally, intention-to-treat and per-protocol analyses will be performed and compared to address cases of protocol noncompliance.

Within the intervention groups, weight loss will be used as the dependent variable, and linear regression model analyses will be performed to estimate the impact of self-monitoring input frequency, WhatsApp group participation, and sociodemographic characteristics as covariates.

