### Eligibility Criteria

The target population will be female merchants between 18 and 65 years of age working in market A with a BMI ≥30 who own a smartphone for personal use and who can use WhatsApp. The exclusion criteria included those who are pregnant or lactating, those who are found pregnant during the intervention period, those for whom weight loss is contraindicated (due to a cancer diagnosis, eating disorders, poorly controlled hypertension, diabetes, etc), and those using physician-prescribed weight loss medication. If they have medical records, we will review them for the eligibility assessment. If they do not, we will ask about their conditions in detail and make a judgment.

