### Recruitment

Four interviewers and supporters will visit the target market, approach potential participants, and screen them to see if they satisfy the inclusion criteria by asking a few questions and taking physical measurements (weight and height measurements). If the participants were eligible, we explained the purpose of the study, the intervention and procedures, and the eligibility and exclusion criteria in detail and returned at least half a day later to obtain their signatures on a consent form. We also explained that the participants would be randomly assigned to either the intervention or control group and would not be able to self-select. We explained that all participants would be weighed regularly at the beginning of the intervention as well as 3, 6, and 12 months later, and that their height would be measured at the beginning of the study so that their BMI would be known each time. We further explained that the control group will have access to free scales placed at several locations in market A 12 months after the end of the entire study, which they can use at their leisure. We also informed them that smartphone apps and other devices would be introduced to them at the end of the study.

Participants could withdraw from the study at any time before data collection at 6 months by submitting a consent withdrawal form to a member of the research team.

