### Outcome

The primary end point of the study is to compare weight changes from baseline to the end of the intervention (6 months later) between the intervention and control groups.

Secondary end points include the differences in body fat percentage, abdominal circumference, stage of behavioral change in weight loss behaviors such as diet and exercise, percentage of individuals with correct weight perception, degree of body pain (with visual analog scale [VAS]), and self-rated health at the end of the intervention (6 months later) compared to baseline. Simultaneously, the intervention group will be evaluated in terms of the frequency of inputs to the self-monitoring apps, degree of participation in WhatsApp groups, average number of steps taken, and degree of weight loss during the intervention period.

To evaluate the interim process of the intervention, the intervention and control groups will be compared and analyzed in the same manner as described above, 3 months after the start of the intervention. In addition, the intervention group will be evaluated for weight change at 1, 2, 4, and 5 months and for changes in the behavioral change stage of weight loss behaviors such as diet and exercise.

As a follow-up evaluation after the intervention, both groups will be evaluated at 12 months (6 months after the end of the intervention) in the same way.

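### The regression on month-6 weight change is labelled intention-to-treat but has no outcome for women who withdraw, are excluded or are lost before month 6, and it leaves the month-3 weight of both arms unused

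*Protocol article*

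**What the plan says.** All references are to the protocol article.

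- **Endpoint (Outcome).** The primary aim is to "compare weight changes from baseline to the end of the intervention (6 months later) between the intervention and control groups".
- **Model (Statistical Methods).** The arms are compared on weight change. In addition, the effect is estimated "using a linear regression model with weight change at 6 months as the dependent variable", with group, stratification variables and sociodemographic attributes as covariates. The opening sentence of that section words the time point differently from the Outcome section. That is a separate matter, and month 6 is taken here as the end of the intervention.
- **Principle (Statistical Methods).** "These analyses will follow the intention-to-treat principles". Further, "intention-to-treat and per-protocol analyses will be performed and compared to address cases of protocol noncompliance".
- **Leaving the trial.** Under Recruitment, "Participants could withdraw from the study at any time before data collection at 6 months by submitting a consent withdrawal form". Under Eligibility Criteria, the exclusions include "those who are found pregnant during the intervention period". A woman can therefore leave after randomisation by at least two routes.
- **Expected loss (Sample Size Calculation).** 10% dropout, with 108 women per group.
- **Available weights.** Under Recruitment, "all participants would be weighed regularly at the beginning of the intervention as well as 3, 6, and 12 months later". Table 2 confirms the month-3 visit weight for both arms. Weights at months 1, 2, 4 and 5 are collected by phone in the intervention arm only.

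The article does not say how a missing month-6 weight is handled. It describes no status of stopping the intervention while remaining in follow-up.

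**The concern.** The named model and the named principle do not fit together once women are lost. Intention-to-treat means that all randomised women count in the arm they were assigned to. A regression on month-6 change can count only those who have that value, unless something is added. The design expects about one woman in ten not to have it.

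The stake is bias more than power. Only the intervention arm receives weekly messages, monthly education and app recording. The trial also deliberately enrols women with little readiness to lose weight: the Background reports that 40.1% of merchant women with obesity in the target market did not wish to. Withdrawal by intervention women who are not losing weight is plausible, and it would make the intervention look better than it is.

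The month-3 visit weight is measured in both arms and says something about where a woman who leaves later was heading. The primary model sets it aside.

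**Working it through.** **1. The plan's sample size.** Inputs from Sample Size Calculation: difference 1.5 kg, SD 3.7 kg, z-values 1.96 and 0.842, dropout 10%.

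- Normal approximation: 2 × (1.96 + 0.842)² × 3.7² / 1.5² = 95.5, so 96 per arm; 96 / 0.9 = 106.7, so 107.
- t-test version: 96.5, so 97 per arm; 97 / 0.9 = 107.8, so 108.

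The stated 108 per group reproduces.

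**2. Power with observed month-6 weights only.** With 108 × (1 − d) women per arm:

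| Loss d | Women per arm | Power |
|---|---|---|
| 0% | 108 | 84.6% |
| 10% | 97.2 | 80.7% |
| 15% | 91.8 | 78.4% |
| 20% | 86.4 | 75.9% |

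The planned 10% is already paid for. What remains at that level is bias.

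**3. Size of the bias.** Let a fraction d of the intervention arm lack a month-6 weight, and let their true mean change be g kg worse than that of the women observed (mean C). The mean of the whole arm is (1 − d) × C + d × (C + g) = C + d × g. Using C alone makes the arm look d × g kg too good. If the control arm loses a fraction d₀ with gap g₀, the net overstatement is d × g − d₀ × g₀.

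With no selective loss among controls (values of d and g assumed):

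| d | g = 1.0 kg | g = 1.5 kg | g = 3.0 kg |
|---|---|---|---|
| 5% | 0.05 | 0.075 | 0.15 |
| 10% | 0.10 | 0.15 | 0.30 |
| 20% | 0.20 | 0.30 | 0.60 |

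A gap of 1.5 kg corresponds to lost women having none of the design effect. At 10% loss the row is 7%, 10% and 20% of 1.5 kg.

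**4. Against sampling error.** With 97 women per arm the standard error of the difference is 3.7 × √(2/97) = 0.53 kg. The central case of 0.15 kg is 0.15 / 0.53 = 0.28 of a standard error.

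**5. What the month-3 weight can add.** If every lost woman had a month-3 weight and data were missing at random, the effective size per arm is 108 / [1 + (d / (1 − d)) × (1 − ρ²)]. Here ρ is the correlation between change at month 3 and change at month 6. It is not in the article and is assumed. For d = 10%:

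| ρ | Effective n per arm | Power |
|---|---|---|
| 0.3 | 98.1 | 81.0% |
| 0.5 | 99.7 | 81.7% |
| 0.7 | 102.2 | 82.6% |
| 0.8 | 103.8 | 83.2% |

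These are upper figures, since women who leave before month 3 add nothing.

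**The case against.** The strongest reply is that the article states no complete-case rule. It names a regression and a principle. Imputation before the regression is compatible with both, and missing-data rules are commonly left to an analysis plan that is not shown. This stands as far as it goes: the restriction to observed month-6 weights is inferred from the model. What remains is that the article itself commits to a single-time-point model for the primary effect, and a better one is available on data already scheduled.

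Four stronger readings are tempting, and the article does not support them.

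- *Withdrawal is the only way out.* It is not, because women found pregnant during the intervention are also excluded.
- *Women who stop the intervention are lost.* This does not follow. Only a submitted form withdraws a woman under Recruitment. Supporters go to the market to weigh participants, engagement with the app and messages is itself analysed, and the per-protocol comparison presupposes that noncompliers stay in the intention-to-treat set.
- *The month-3 weight would retain most women who are lost.* The article does not say when loss is expected or whether data are kept after consent is withdrawn.
- *The effect will be overestimated.* The direction depends on which arm loses whom. Controls wait until after month 12 for scales and the app and may also leave. Similar selective loss in both arms would largely cancel.

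It is also fair to say that a mixed model does not remove bias when women leave for reasons that their earlier weights do not show.

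**Conclusion.** The point holds in a limited form. As written, the primary effect model cannot include women without a month-6 weight, although the analyses are called intention-to-treat and 10% loss is planned. It also ignores a weight measured in both arms at month 3.

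The possible overstatement is modest: 0.15 kg at 10% loss in the intervention arm and a 1.5 kg gap, or 0.10 to 0.30 kg for gaps of 1 to 3 kg. This assumes no selective loss among controls, and both the arm split and the gap are assumptions. The gain in power from using month 3 is small, from 80.7% to between 81.0% and 83.2% at best. The sample size is sound. This is a low-cost improvement and no ground for doubting the design.

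**What to change.** **Statistical Methods.** Estimate the month-6 contrast from a mixed model for repeated measures on the visit weights taken in both arms, with arm by visit, baseline weight and the stratification variables. Include every randomised woman with any post-baseline visit weight whose data may be retained. Exclude the phone weights at months 1, 2, 4 and 5 from this model and from any imputation, because they have no control counterpart.

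**Recruitment.** State that a woman who stops the calls, messages or app without withdrawing consent to measurement is still weighed at the planned visits. This matters more than the choice of model, because an observed month-6 weight needs no assumption.

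**Cost.** No new visits and no change in sample size. Under Ethical Considerations a protocol change is notified to the ethics committee and the registry. Because the trial is unblinded, the change should be dated before month-6 weights are compared by arm. The model relies on data missing at random, does not recover women who leave before month 3, and may give a slightly less favourable estimate.

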**Data collection for intervention group and control group**																					
	Weight, body fat percentage, and abdominal circumference measurements	✓				✓						✓						✓		✓	
	Height measurement	✓																			
	Structured interview	✓				✓						✓						✓		✓	

^a^The intervention lasted from months 0 to 6.

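### The comparison that appears to decide the primary outcome names no covariates, although randomisation is stratified by BMI and age and baseline weight is measured; one adjusted model should be named as primary

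*Protocol article*

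**What the plan says.** The Outcome section sets the primary endpoint: to "compare weight changes from baseline to the end of the intervention (6 months later) between the intervention and control groups". The Statistical Methods section then describes two analyses.

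- First: "The primary outcome will be evaluated by comparing the difference in weight change between the intervention and control groups". No test, model or covariate is named.
- Second: "In addition, the effectiveness of the weight loss intervention will be estimated using a linear regression model". Baseline weight is not among its named terms, and the sociodemographic attributes are not listed one by one; the specification reads "weight change at 6 months as the dependent variable and the affiliation group, stratification variables, and other sociodemographic attributes as covariates".

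Neither analysis is called primary, supportive or sensitivity. The same section carries the approach over to body fat percentage, abdominal circumference and pain VAS at 3, 6 and 12 months.

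On the design side, "Stratification will be conducted based on BMI (threshold: 32 kg/m^2^) and age (threshold: 45 years"). Table 2 schedules "Weight, body fat percentage, and abdominal circumference measurements" at month 0 as well as at screening and at 3, 6 and 12 months, so a continuous baseline weight will be on file.

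The Statistical Methods sentence, read literally, places the comparison six months after the intervention ended. I take month 6, as in the Outcome section; that wording needs reconciling, but it is a separate matter.

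**The concern.** Stratified randomisation balances BMI and age between arms, which removes their contribution from the sampling variation of the treatment difference. A plain two-group comparison still counts that contribution in its standard error. If the strata are prognostic, the interval is too wide, the test is conservative and the trial gives up power that its own design has provided. The planned regression includes the strata, but it appears as an addition and not as the deciding analysis.

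Baseline weight is the obvious covariate for a weight outcome. It is measured, yet the only body-size term in either analysis is the BMI stratification variable. The text does not say whether that enters as the two-level stratum or as a continuous value. Without baseline weight in the model, chance imbalance in it stays in the estimate.

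At stake are some power in a trial planned at 80%, and clarity about which result will be reported as the answer. Validity is not at stake.

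**Working it through.** **Inputs from the Protocol article (Sample Size Calculation):** difference 1.5 kg, SD 3.7 kg, z = 1.96 and 0.842, dropout 10%, 108 per arm. The documents do not give the variance explained by the strata, the SD of baseline weight, or its correlation with change or BMI. Values for these are assumptions, shown as ranges.

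**1. The stated sample size.** n = 2 × [3.7 × (1.96 + 0.842) / 1.5]² = 95.5, so 96 per arm; 96 / 0.9 = 106.7, so 107. The t-test version gives 97 per arm; 97 / 0.9 = 107.8, so 108. The figure reproduces, and it is the size for an unadjusted comparison of two means. With 97 evaluable per arm, SE = 3.7 × √(2/97) = 0.531 kg and power is Φ(1.5/0.531 − 1.96) = 80.6%.

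**2. Cost of ignoring the strata.** Let the strata explain a share R² of the variance of change, and let the arms be balanced on them. The true SE is then 0.531 × √(1 − R²), while the simple test still uses 0.531.

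- Size of the simple test = 2 × [1 − Φ(1.96 / √(1 − R²))]
- Power of the simple test = Φ[(1.5/0.531 − 1.96) / √(1 − R²)]
- Power of the adjusted test = Φ[1.5 / (0.531 × √(1 − R²)) − 1.96]

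| Assumed R² | Size, simple | Power, simple | Power, adjusted |
|---|---|---|---|
| 0.05 | 4.4% | 81.2% | 82.6% |
| 0.10 | 3.9% | 81.9% | 84.5% |
| 0.20 | 2.8% | 83.3% | 88.4% |

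Simulations of a four-stratum permuted-block design (block size 4 assumed where it was set) give sizes of 4.4–4.7%, 3.8–3.9% and 2.8–3.0%, in line with the formula. The power given up is about 1, 3 and 5 percentage points.

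**3. Added gain from baseline weight.** Assume equal SDs S at baseline and month 6. Then ρ = 1 − 3.7² / (2S²), and the variance of the baseline-adjusted estimate relative to the change score is (1 + ρ)/2.

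- S = 10 kg: ρ = 0.932, ratio 0.966
- S = 15 kg: ρ = 0.970, ratio 0.985

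These ratios correspond to a correlation between change and baseline of 3.7/(2S), or 0.12–0.19 in absolute value. If that correlation were 0.2–0.4, power with 97 per arm would be 82.2–86.9%.

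These gains are measured against a model without BMI. A median-split BMI stratum captures a share (BMI–weight correlation)² × 2/π of what weight explains. That is 31–46% for an assumed correlation of 0.7–0.85, so the extra gain in the planned regression is smaller.

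**The case against.** The hierarchy can be read from the text. The first analysis is the one tied to the primary outcome, the regression is introduced as an addition, and 108 per arm reproduces from the simple comparison. This stands: the ranking is implied, though not stated.

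A reader might infer stronger faults that the document does not support.

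- **Inflated type I error.** If either analysis could be claimed and their correlation were √(1 − R²), the either-of-two error would be 6.0%, 6.5% or 7.1% for R² of 0.05, 0.10 or 0.20. The article does not say that either result may be claimed. The formula also needs all of R² to come from covariates left to chance balance, whereas BMI and age are balanced by design. With variance from the strata alone, simulated error is about 4.8–5.5%. With 5% from strata and 5% from other covariates it is about 5.8–5.9%.
- **Covariates chosen after seeing the data.** This is a condensed article. Listing individual covariates is commonly left to the full protocol or analysis plan, which are not shown.
- **Women without a month-6 weight are dropped.** The article states intention-to-treat principles and does not specify a complete-case analysis. Handling of missing weights is likewise analysis-plan detail.
- **Omitting baseline weight biases the result.** It does not. A change score already subtracts baseline, and both analyses are unbiased under randomisation.

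It is also fair to say that an SE that is too large cannot favour a false claim of benefit, and that the planned regression already contains the strata. What remains is that the analysis that appears to decide leaves the stratification factors out, and that no label settles the matter.

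**Conclusion.** The point holds as a matter of efficiency and clarity. As written, the comparison that seems to be primary names no adjustment for the factors used to stratify randomisation, or for baseline weight. If the strata explain 5–20% of the variance of weight change (assumption), the test runs at about 4.7% down to 2.8% instead of 5% and gives up roughly 1 to 5 points of power. If the strata are not prognostic, the loss is nil. Baseline weight adds a modest gain, a variance ratio of about 0.97–0.98 for an assumed SD of 10–15 kg and less once BMI is in the model. That the first comparison is unadjusted is itself an inference from the absence of any named covariate. The trial remains valid and 108 per arm need not rise.

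**What to change.** In Statistical Methods, name one primary analysis: a linear model of month-6 weight (or change to month 6) on arm, continuous baseline weight, and the BMI and age stratification factors. State whether those factors enter as strata or as continuous values. Label the unadjusted comparison and the regression with sociodemographic attributes as sensitivity analyses. Use the same form, each with its own baseline value, for body fat percentage, abdominal circumference and pain VAS.

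A repeated-measures model over the 3-, 6- and 12-month weights is an option, not a requirement.

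The cost is wording in the protocol and analysis plan, settled before outcome data are examined by arm. For the primary model, every variable is already scheduled for collection, and the sample size is unchanged.
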